##### Sample Size

We calculated the sample size based on the difference we expect in the primary outcome (ie, PrEP uptake) by month 9. A sample size of 121 per group achieves 90% power to detect a 10% increase in PrEP uptake for the JomPrEP group compared with the TAU group, assuming 50% PrEP uptake in the TAU group at the 1-sided .05 significance level. A sample of 268 participants will be enrolled and randomized to the JomPrEP and TAU groups to accommodate a 10% dropout. Assuming 60% of PrEP uptake in the JomPrEP group, this sample size provides 85% power in detecting a standardized effect size of 0.5 for the secondary outcomes of adherence and persistence.

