#### Phase IIA: Efficacy Trial of JomPrEP

##### Study Design

We will conduct a prospective randomized controlled trial to evaluate the efficacy of JomPrEP versus treatment as usual (TAU) among MSM in Malaysia for primary (ie, HIV testing and PrEP uptake) and secondary (ie, PrEP adherence and persistence) outcomes over 9 months of observation. We will enroll 268 participants who will be randomized (1:1) to receive either JomPrEP or TAU and will be followed for 9 months (assessments at 3, 6, and 9 months; Figure 1).

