##### Primary Outcomes

All structured interviews will be assessed online via Qualtrics (Qualtrics XM). Primary outcomes are those along the HIV prevention cascade, including uptake of HIV testing (ie, ordering of HIV self-testing kit and uploading the result via the app or HIV testing as part of the PrEP clinical care) and PrEP (ie, current use of PrEP; yes/no). Both HIV testing and PrEP uptake will be assessed at each follow-up time point (3, 6, and 9 months) using self-report and medical record review for confirmation.

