##### Analytical Plan

To test the hypothesis that the intervention group (I=JomPrEP) will be significantly more effective than the TAU group for HIV testing and PrEP uptake, we will compare the proportion for both outcomes. The null hypothesis is that the proportion of HIV testing and PrEP uptake in the intervention group and TAU is equal, expressed as follows: H_0_: p_I_=p_TAU_, where p_I_ and p_TAU_ are the proportion of HIV testing and PrEP uptake in the JomPrEP and TAU groups, respectively. Our alternative hypothesis is H_1_: p_I_>p_TAU._ We will use both intent-to-treat (ITT) and on-treatment analyses, with ITT used for efficacy. Baseline characteristics will be tested for homogeneity across the 2 groups using a *t* test or Wilcoxon rank sum test for continuous variables and chi-square test or Fisher exact test for categorical variables. Any baseline variable showing a significant difference at *P*<.05 between the 2 groups will be put into the model for adjustment. For all outcome variables assessed over a 9-month follow-up period, plots of longitudinal data over time will be provided. Prior to the primary analysis, the distribution of the missing data pattern will be examined across the 2 groups. For a subgroup of those starting PrEP, we will compare PrEP adherence using the same method and PrEP persistence using time-to-discontinuation and Cox proportional hazards ratios.

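### The protocol tests two primary outcomes in some sections and sizes the trial on one in another, with no stated rule for what counts as success

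*Protocol article*

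**What the plan says.** Four places in the Protocol article bear on this.

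- Study Design (Phase IIA) sets up the comparison "for primary (ie, HIV testing and PrEP uptake) and secondary (ie, PrEP adherence and persistence) outcomes", so two outcomes are primary.
- Primary Outcomes uses the plural and defines both. HIV testing counts either a self-test ordered and uploaded or a test done within PrEP care. PrEP uptake is "current use of PrEP; yes/no". Both are assessed at 3, 6 and 9 months.
- Analytical Plan writes one null and one one-sided alternative, whose two proportions "are the proportion of HIV testing and PrEP uptake in the JomPrEP and TAU groups". It then refers to primary hypotheses in the plural and contrasts both proportions at the 9-month follow-up from a generalized linear mixed model.
- Sample Size states: "We calculated the sample size based on the difference we expect in the primary outcome (ie, PrEP uptake) by month 9". It assumes 50% in the TAU group and 60% in the JomPrEP group, 90% power and 121 per group, "at the 1-sided .05 significance level".

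That .05 is the only significance level given for an efficacy comparison, and it is attached to PrEP uptake. The other .05, in Analytical Plan, concerns baseline comparisons. No level is given for HIV testing.

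**The concern.** The number of primary outcomes decides how the type I error is spent and what a positive trial means. Here one section spends all of it on PrEP uptake, while others run a second primary test of HIV testing. The single pair of proportions cannot represent two different outcomes, so the hypothesis does not say what has to be shown. A trial with one outcome significant and the other not could be reported as positive or negative, and nothing in the article settles which.

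A smaller point concerns timing. The outcome definition and the model contrast use current PrEP use at the 9-month visit. The Sample Size section speaks of a difference by month 9, which could also mean ever having started. Someone who starts and stops PrEP is a success under one reading and a failure under the other.

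**Working it through.** **1. Number of primary outcomes.** Study Design: two. Primary Outcomes: two, each defined. Analytical Plan: two tested, one shared hypothesis. Sample Size: one, PrEP uptake. These cannot all be right.

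**2. Error if either outcome suffices.** Inputs: one-sided .05 for each test (stated for PrEP uptake, assumed for HIV testing) and a bivariate normal pair of test statistics with correlation ρ under both nulls. The critical value is 1.645.

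P(at least one false positive) = 0.05 + 0.05 − P(both Z > 1.645)

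| ρ | P(both) | P(at least one) |
|---|---|---|
| 0 | 0.0025 | 0.0975 |
| 0.3 | 0.0071 | 0.0929 |
| 0.5 | 0.0122 | 0.0878 |
| 0.7 | 0.0196 | 0.0804 |
| 0.9 | 0.0319 | 0.0681 |

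The independent case is 1 − 0.95² = 0.0975. A test done within PrEP care counts as HIV testing, so positive correlation is likely and 9.75% is the upper end.

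**3. Error if both are required.** The chance of a false claim is then at most .05, so there is no inflation. Joint power is at most the smaller of the two powers.

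**4. Power for the outcome used for sizing.** This bears on the choice of rule. Inputs from Sample Size: 0.50 versus 0.60, one-sided .05, 90% power. The mean proportion is 0.55.

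n = [1.645·√(2·0.55·0.45) + 1.282·√(0.25 + 0.24)]² / 0.10² = [1.645·0.7036 + 1.282·0.70]² / 0.01 ≈ 422.03, so 423 per group.

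The stated figure is 121, which is not reproduced. At 121 per group:

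power = Φ[(0.10·√121 − 1.645·0.7036) / 0.70] = Φ(−0.082) = 46.7%.

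The dropout step is consistent: 242/0.9 = 268.9, against 268 stated.

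With the alpha split evenly (one-sided .025 each), the same formulas give 519 per group for 90% power, and 34.5% power at 121.

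**5. The month 9 wording.** Primary Outcomes and Analytical Plan together give current use at the 9-month visit. Sample Size reuses the same term without redefining it, but then takes 60% uptake as the basis for power on adherence and persistence, which apply to those who initiated PrEP. As a reconstruction, 60% of 121 is about 73. With 73 in each group and a standardized effect of 0.5, a two-sided .05 t test has 85.1% power, close to the stated 85%. This assumes 73 in both groups, although the TAU rate is 50%. It suggests that uptake may stand for initiation there, but does not prove it.

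**The case against.** A reader might infer that the plan runs two tests at one-sided .05 and lets either one carry the efficacy claim, so that the error is simply 9.75%. The documents do not support that. No level is stated for HIV testing, and the shared hypothesis gives only a direction. The hypothesis joins the two outcomes with *and*, as does the Discussion, so a both-must-succeed reading is open, and under it nothing is inflated. Independence is also the least plausible correlation, given how HIV testing is defined.

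A reader might also infer that error control is absent altogether. A condensed article commonly leaves multiplicity to the full protocol or SAP, which are not shown, so its absence here is not itself an error. This stands. It does not remove the conflict: an unseen hierarchy would not make the Sample Size section agree with the other three.

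On timing, *by month 9* can simply mean the difference expected at that point. That also stands. Any figure for how far ever-started and currently-using would differ needs a stopping rate that the article does not give, and a shift in level within one arm would not show an effect on the between-group difference.

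Finally, a fixed sequence is one choice among several, and it demotes a declared primary outcome. That is a design decision and more than an edit of wording.

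**Conclusion.** The conflict over one or two primary outcomes is in the text, and no success rule is stated. Its consequence is conditional. If either outcome suffices and both are tested at one-sided .05, the familywise one-sided error is about 6.8% to 9.75% for correlations from 0.9 down to 0. If both must succeed, the error is held but joint power is capped at that of the weaker test. Under the plan's own assumptions that cap is no higher than about 47%, the power for PrEP uptake at 121 per group. The timing phrase is an ambiguity to clear up, not a demonstrated error. The point should be corrected before outcome data by group are seen. It does not show that the trial will exceed its error rate.

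**What to change.** Make Study Design, Primary Outcomes, Analytical Plan and Sample Size agree on the number of primary outcomes. Write a separate null and alternative for each outcome, and state one success rule that holds the overall one-sided error at .05.

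One workable rule is a fixed sequence: PrEP uptake first at the full one-sided .05, because it is the outcome used for sizing, then HIV testing at the same level only if PrEP uptake is significant. This takes no alpha from PrEP uptake and needs no added participants to control the error.

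The cost is that HIV testing becomes gated. If the true difference in PrEP uptake is the assumed 10 points, 121 per group passes the gate only about 47% of the time, so an HIV testing claim would be blocked in roughly half of such trials however strong that effect. The sample size figure therefore needs to be reconciled before the rule is chosen.

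Two alternatives are acceptable:

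- Holm's procedure has no gate. Its first step is at one-sided .025, where PrEP uptake has about 34.5% power at 121 per group. Power recovers towards 46.7% only if HIV testing is significant first.
- Requiring both outcomes needs no alpha split, but pays in joint power.

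Reword Sample Size to current use at the 9-month visit, matching Primary Outcomes and Analytical Plan, and report ever having initiated by month 9 as supportive. That part is wording only. Current use still reflects both starting and staying on PrEP, and the supportive result helps to separate the two.

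### The stated 90% power for 50% versus 60% PrEP uptake is wrong: 121 per group gives about 47%, and 90% needs about 420 per group

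*Protocol article*

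**What the plan says.** The Sample Size section names PrEP uptake as the sizing outcome: "We calculated the sample size based on the difference we expect in the primary outcome (ie, PrEP uptake) by month 9". It then claims: "A sample size of 121 per group achieves 90% power to detect a 10% increase in PrEP uptake for the JomPrEP group". The sentence goes on to give the other inputs: "assuming 50% PrEP uptake in the TAU group" and "at the 1-sided .05 significance level". Two sentences later, the calculation for the secondary outcomes begins "Assuming 60% of PrEP uptake in the JomPrEP group", which fixes the 10% as an absolute difference. Enrolment is set with a dropout allowance: "A sample of 268 participants will be enrolled and randomized to the JomPrEP and TAU groups to accommodate a 10% dropout".

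The Study Design section confirms equal allocation: "We will enroll 268 participants who will be randomized (1:1) to receive either JomPrEP or TAU". The Analytical Plan states a one-directional superiority hypothesis ("Our alternative hypothesis is H_1_: p_I_>p_TAU"). It compares the two proportions at the 9-month follow-up by a linear contrast from a generalized linear mixed model.

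**The concern.** A 10-point difference around 50%, where the binomial variance is largest, normally needs several hundred participants per group for 90% power. A figure of 121 per group is far below that, even with a one-sided 5% test.

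PrEP uptake is the outcome on which the trial is sized. If the true power is near one half, the trial is about as likely to miss its target effect as to find it. Anyone relying on the published 90% could then read a non-significant result as evidence that a 10-point gain does not exist, when the trial was never large enough to support that.

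**Working it through.** **Inputs, all from the protocol article**
- TAU uptake p₁ = 0.50, JomPrEP uptake p₂ = 0.60, one-sided α = 0.05, power 90%, n = 121 per group (Sample Size)
- 1:1 allocation, 268 enrolled, so 134 per group (Study Design, Sample Size)
- Test: comparison of proportions at 9 months (Analytical Plan)
- Normal quantiles: 1.645 for α, 1.282 for 90% power

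**1. Attempt to reproduce the stated 90% at n = 121**

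Unpooled variance:
- Standard error = √[(0.25 + 0.24)/121] = 0.0636
- Power = Φ(0.10/0.0636 − 1.645) = Φ(1.571 − 1.645) = Φ(−0.073) = 47.1%

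Other forms at 121 per group:

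| Calculation | Power |
|---|---|
| Pooled variance under the null | 46.7% |
| Arcsine | 46.9% |
| Exact binomial power of the z test | 48.0% |
| Fisher exact test | 42.9% |
| Two-sided 5% (pooled) | 34.5% |
| Relative reading, 50% vs 55% (pooled) | 19.3% |

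With all 134 per group evaluable, pooled power is 50.0%. The stated 90% is not reproduced by any of these.

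**2. Sample size for 90% power**
- Unpooled: n = (1.645 + 1.282)² × (0.25 + 0.24)/0.10² = 8.564 × 49 = 419.6, so 420 per group
- Pooled: n = [1.645√(2 × 0.55 × 0.45) + 1.282√0.49]²/0.10² = 422.0, rounding up to 423 per group
- Arcsine 423; continuity-corrected 442

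These are evaluable numbers. Allowing for 10% dropout, 423/0.90 = 470 per group, or 940 in total. The stated 121 is under a third of the requirement (121/420 = 0.29).

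**3. What 121 per group can detect from a 50% TAU rate (pooled, one-sided 5%)**
- 90% power: about 18.3 points (50% vs about 68%)
- 80% power: about 15.7 points (50% vs about 66%)

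**4. Could the repeated visits make up the gap?**

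Suppose the test averaged m measurements per person with within-person correlation ρ. The required n would then be multiplied by [1 + (m − 1)ρ]/m. No ρ is given in the article, so the values below are assumptions.

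| m | ρ | Power at 121 per group (pooled) |
|---|---|---|
| 3 | 0 | 85.7% |
| 3 | 0.5 | 60.7% |
| 4 | 0 | 93.2% |
| 4 | 0.05 | 89.9% |
| 4 | 0.5 | 63.1% |

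The three follow-ups fall short of 90% even with no correlation at all. Only four measurements with ρ of about 0.05 or less reach it.

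**5. Is 121 really per group, and is 60% really intended?**

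121 × 1.1 = 133.1, rounded up to 134, and 2 × 134 = 268, so 121 is per group. With 134 per group, 50% and 60% uptake give about 67 and 80 PrEP starters. A standardized effect of 0.5 then has about 85.5% power, taking a two-sided 5% test (an assumption). That is close to the 85% stated for the secondary outcomes, which suggests that 50% and 60% were the working rates.

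**The case against.** The best defence is that 121 may come from a repeated-measures formula whose inputs the article omits. Questionnaires are given at baseline and at 3, 6 and 9 months, and the primary model is a mixed model for repeated measurements. With four measurements and a correlation of 0.05, the unpooled formula gives 419.6 × (1 + 3 × 0.05)/4 = 120.6, which rounds up to exactly 121. On that view the fault is a mismatch between the sizing method and the test rather than an arithmetic slip.

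This may explain where 121 came from, but it does not support the claim:
- The correlation of 0.05 appears nowhere in the article.
- Eligibility excludes existing PrEP users, so the baseline measurement carries no information on the outcome.
- Sizing is on uptake by month 9 and the test is the 9-month contrast, not a time average.
- Current PrEP use in the same man at successive quarterly visits is unlikely to be almost uncorrelated.

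A second objection stands in part. The article does not show whether the rates, the effect or the sample size was misreported, and nothing in it supports an expected effect of 18 points. That figure should therefore be reported as what the size can detect, not adopted as a new expected effect.

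An article may leave the details of a sample size method to a fuller document. That does not excuse a stated power that conflicts with the inputs printed beside it.

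**Conclusion.** The power statement is wrong as written and must be corrected. For 50% versus 60% at one-sided 5%, 121 per group gives about 47% power against the 90% claimed, a shortfall of about 43 percentage points. Full retention of 134 per group raises it only to 50%. Ninety per cent power needs 420 to 423 evaluable per group.

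The conclusion rests on the article's own rates, alpha, allocation and 9-month comparison, with independent participants. The section on minimizing contamination says couples and housemates are randomised together; any positive correlation within those pairs would lower power further, so 47% is if anything generous. Which input caused the error cannot be determined from the article.

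**What to change.** Replace the power sentence with one that follows from its inputs, for example: *With 121 evaluable participants per group and a one-sided .05 test, power is about 47% for PrEP uptake of 50% versus 60% at month 9; the same size gives 90% power for 50% versus about 68% and 80% power for 50% versus about 66%.* Justify the sample size by that detectable difference, labelled as such and not as the expected effect. State the method and inputs that produced 121, and reconcile them with the 9-month contrast. Say explicitly that a non-significant result does not exclude a 10-point benefit, and commit to reporting the difference in uptake with its confidence interval.

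The cost is wording in the protocol and analysis plan, plus a less favourable stated power; the correction itself needs no extra participants. If the sponsor instead wants to keep 90% power for 10 points, the trial would need about 470 enrolled per group (940 in total) at 10% dropout, which is a separate decision.

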## Introduction

Reductions in HIV incidence and mortality have not translated uniformly on a global scale, especially in many Southeast Asian countries and among sexual minority groups, where stigma and discrimination are high [1-3]. In Malaysia, same-sex sexual behavior is illegal in both secular and Sharia laws, translating to high levels of stigma and discrimination. With over 100,000 cumulative HIV cases, Malaysia’s rapidly expanding HIV epidemic is the fifth largest in the Asia-Pacific region and has now transitioned into men who have sex with men (MSM). From 2008 to 2018, MSM accounted for an increasing proportion of incident HIV cases (10%-21.6%), with trends among this population projected to rise even more in the coming years, making MSM the primary key population with the highest HIV prevalence in Malaysia through 2030 [4,5]. Central to this expanding HIV epidemic among MSM is condomless sex, sexually transmitted infections, and co-occurring psychiatric and substance use disorders [6-9].

Modeling studies for MSM suggest that pre-exposure prophylaxis (PrEP) is a highly effective strategy to avert new HIV infections [10-18]. PrEP uptake, however, is low among Malaysian MSM despite acknowledged high risk and strong interest in taking it [19,20]. Multilevel factors undermine the scale-up of HIV testing and subsequent linkage to PrEP services among Malaysian MSM. Patient-level factors are MSM’s hesitancy to disclose their sexuality or risk behaviors in-person to providers, primarily due to fear of stigma, discrimination, or criminalization. Furthermore, findings from other studies expanded these factors to include additional patient- (eg, mental illness, negative experiences with clinicians, low perceived HIV risk), provider- (eg, stigma and discrimination), and structural-level (eg, multiple clinic visits, long waits, lack of after-hour clinic visits) barriers [21-29]. Therefore, the scale-up of HIV testing and PrEP to individuals most at risk for HIV infection requires innovations to support this marginalized group.

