### Theoretical Framework

The HealthMindr app is based on the Social Cognitive Theory (SCT) [40], which asserts that cognition, behavior, and environmental influences interact with and reinforce one another to impact health behavior. It specifies goal setting, self-efficacy, outcome expectations, and self-regulation as essential influences of health behavior. Features in HealthMindr fit the framework for several health behaviors such as making HIV testing plans, consistently using condoms, screening for PrEP, and seeking PrEP (if eligible). For each health behavior, there are specific app features designed to promote goal setting, self-efficacy, outcome expectations, and self-regulation. For example, for HIV testing, the “Make a Plan” feature promotes goal setting. The presentation of several testing options and information promotes self-efficacy, while information about the benefits of testing promotes positive outcome expectations, and a customizable reminder is used for testing self-regulation. HealthMindr has shown preliminary acceptability and usability among MSM in the United States [37], and HealthMindr combined with in-app prevention messages doubled HIV testing and PrEP uptake in a randomized trial among MSM in the United States [41]. As JomPrEP will be adapted from HealthMindr, its main domains will coincide with the core elements of the SCT framework.

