##### Study Settings and Participants

Eligibility screening and recruitment will be identical to procedures used for phase I. We will partner with the Centre of Excellence for Research in AIDS (CERiA) at the University of Malaya, Kuala Lumpur, Malaysia. Eligibility criteria will include the following: (1) age ≥18 years; (2) cis-gender men; (3) laboratory-confirmed HIV negative status; (4) no existing use of PrEP; (5) own a smartphone; and (6) ability to understand, read, and speak English. Participants will be discontinued from the study under any of these circumstances: (1) acquisition of HIV infection (will be referred to appropriate care); (2) participant voluntarily chooses to leave the study; and (3) the provider thinks the study is no longer in the best interest of the participant.

Participants will be recruited using both in-person and online recruitment strategies. For in-person recruitment, flyers will be given out to potential participants as well as posted at local community-based organizations. In addition, various general and MSM-specific social media and other online platforms will be chosen as venues for participant recruitment. These include placing advertisements in geosocial networking apps popular among MSM in Malaysia (eg, Grindr, Hornet) as well as posting study flyers on Malaysian MSM–focused Facebook pages. The recruitment materials will include brief information about the study and contact information (and a link to the study website) where potential participants could receive more information.

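### The 85% power for adherence and persistence rests on 50% control-arm PrEP uptake, a rate in tension with the protocol's own account; the 90% primary figure is missed at 50% and at the lower rates tried

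*Protocol article*

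**What the plan says.** The Sample Size section of the protocol article makes two power claims.

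- Primary (PrEP uptake by month 9): "A sample size of 121 per group achieves 90% power to detect a 10% increase in PrEP uptake", "assuming 50% PrEP uptake in the TAU group at the 1-sided .05 significance level". Enrolment is 268 to allow for 10% dropout.
- Secondary: "Assuming 60% of PrEP uptake in the JomPrEP group", the same sample is said to give 85% power for a standardized effect of 0.5 on adherence and persistence. The Secondary Outcomes section limits both to participants who initiated PrEP.

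Elsewhere the article describes what should be expected under usual care:

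- Introduction: "PrEP uptake, however, is low among Malaysian MSM despite acknowledged high risk and strong interest in taking it".
- Study Settings and Participants: entry requires "no existing use of PrEP".
- Procedures: the TAU group has the app with its main functions switched off, keeping an information library and a chat line to research staff.
- Primary Outcomes: PrEP uptake is defined as current use at each visit.

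**The concern.** The trial's rationale is that few men in this population take PrEP under existing services. The sizing nevertheless expects half of a PrEP-naive control group, without the app's PrEP pathway, to be using PrEP at month 9, and offers no reasoning for it.

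The secondary outcomes have most at stake. Their denominator is the number of men who start PrEP, and that number is set by the uptake rates in the two arms. If TAU uptake is well below 50%, there will be far fewer starters than the 85% figure needs. A null result on adherence or persistence could then be read as evidence of no difference when the comparison was close to descriptive. Correcting the primary calculation alone would not reveal this, because the 85% figure is arithmetically reproducible once 50% is accepted.

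**Working it through.** **Inputs from the document.** One-sided alpha .05; 121 per group evaluable; 268 enrolled 1:1, so 134 per arm; 10% dropout (134 × 0.9 ≈ 121); TAU 50%, JomPrEP 60%; standardized effect d = 0.5 in PrEP starters.

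**Assumed inputs.** The document gives no lower control rate, so 40%, 30%, 20%, 10% and 5% are illustrations. The 10-point gain is kept unless stated otherwise. Starters per arm are taken as n × uptake.

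**Primary outcome: the plan's own figure.** Two-proportion z-test with pooled null variance:

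Power = Φ[(δ − 1.645·SE0)/SE1], with SE0 = √[2p̄(1−p̄)/n] and SE1 = √{[p1(1−p1) + p2(1−p2)]/n}.

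For 50 v 60 and n = 121: p̄ = 0.55, SE0 = 0.0640, SE1 = 0.0636. Power = Φ[(0.10 − 1.645 × 0.0640)/0.0636] = Φ(−0.08) = 47%. The stated 90% does not reproduce; it would need 423 per group.

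**Primary outcome at other control rates, n = 121 per group.**

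| TAU v JomPrEP | SE0 | SE1 | Power |
|---|---|---|---|
| 50 v 60 | 0.0640 | 0.0636 | 47% |
| 20 v 30 | 0.0557 | 0.0553 | 56% |
| 10 v 20 | 0.0459 | 0.0455 | 70% |
| 5 v 15 | 0.0386 | 0.0380 | 83% |

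For a fixed 10-point gain, power rises as the control rate falls, because binomial variance is largest near 50%. It reaches about 90% only at a TAU rate near 3%.

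**Secondary outcomes: the plan's own figure.** Two-sample t-test, noncentrality λ = 0.5/√(1/n1 + 1/n2), with n1 + n2 − 2 degrees of freedom. With 134 per arm and no dropout, starters are 134 × 0.5 = 67 and 134 × 0.6 ≈ 80. Then λ = 3.02 and two-sided .05 power is 85.1%, which matches the stated 85%. One-sided, the same inputs give about 91%.

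**Secondary outcomes after the planned dropout, 121 per arm.**

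| Uptake TAU/JomPrEP | Starters (TAU + JomPrEP) | λ | Two-sided power | One-sided power |
|---|---|---|---|---|
| 50/60 | about 60 + 73 = 133 | 2.87 | 81% | 89% |
| 40/50 | about 48 + 60 = 108 | 2.59 | 73% | 82% |
| 30/40 | about 36 + 48 = 84 | 2.28 | 61% | 73% |
| 20/30 | about 24 + 36 = 60 | 1.91 | 47% | 59% |
| 10/20 | about 12 + 24 = 36 | 1.42 | 28% | 40% |

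Ignoring dropout does not rescue the figure at low rates: with 134 per arm, two-sided power is 51% at 20/30 and 31% at 10/20.

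**If only the TAU rate falls and JomPrEP stays at 60%.** At 30/60 with 121 per arm, primary power is above 99%. The secondary comparison has about 36 + 73 starters and about 68% two-sided power (79% one-sided). The two claims therefore respond to the control rate in opposite directions.

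**The case against.** **The document does not contradict its 50%.** A reader might infer that it does. It gives no numeric uptake rate. The Introduction describes the wider community and also reports strong interest in PrEP, whereas the sizing concerns volunteers for an HIV-prevention study over 9 months, who still get information and a chat line. Starting from no PrEP use is true of any initiation trial and does not fix the month-9 rate. This stands, and it limits the point to a tension. The missing source alone would not be a finding either, since an article condenses a fuller protocol.

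**A lower control rate helps the primary analysis.** A reader might infer that 50% flatters primary power. It does the reverse: for a 10-point gain, 50% is close to the least favourable rate. The primary shortfall comes from the arithmetic, not from the choice of 50%.

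**The parent-app result does not set the effect size.** The Theoretical Framework says the parent app, combined with in-app messages, "doubled HIV testing and PrEP uptake in a randomized trial among MSM in the United States". A reader might conclude that the plan should assume a doubling, or specifically 10% v 20%. No rates are given for that trial, it tested another app in another country, and the Sample Size section does not claim to rely on it. Planning for a smaller relative effect (60/50 = 1.2) is not an error.

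**The secondary statement does not repeat the 50%.** It names only the 60% in the JomPrEP arm. The dependence on 50% is inferred from the comparison needing starters in both arms and from 67 and 80 starters giving 85%. Taking 60% in both arms with 121 per arm (about 73 starters each) also gives about 85% two-sided, but that puts TAU uptake above the plan's own assumption.

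**Starters may outnumber current users.** The primary endpoint is current use, so men who start and stop would still enter the adherence and persistence set. That would soften the fall in power by an amount the document does not allow one to estimate.

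**Conclusion.** The point holds in a limited form. The 50% TAU rate sits uneasily with the article's own description of the population and the control condition, but it is not shown to be wrong.

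The 85% secondary claim is sensitive to that rate. At the plan's 50% and 60% it is met two-sided only if nobody drops out; after the planned dropout it is about 81% two-sided (89% one-sided). At lower assumed control rates with a 10-point gain it falls to roughly 28% to 61% two-sided (40% to 73% one-sided) over 10/20 to 30/40.

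The 90% primary claim is missed at the planned rates (47%) and at 20 v 30, 10 v 20 and 5 v 15 (56% to 83%). A lower control rate narrows that gap.

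These results rest on illustrative lower rates, equal dropout in both arms, starters counted as n × uptake, and single two-group comparisons rather than the planned repeated-measures or Cox models.

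**What to change.** Keep N=268 and revise the Sample Size section.

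1. Give the reasoning for the TAU rate in PrEP-naive Malaysian MSM, or replace the single 50% with a table over control rates of about 5% to 50%.
2. In that table show, after 10% dropout, the primary power and the expected number of PrEP starters in each arm.
3. Restate the 90% and 85% figures from the table, saying for each whether the test is one-sided or two-sided and whether dropout has been applied.
4. If the expected starters do not support the stated power, describe adherence and persistence as exploratory.

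Do not tie the target difference to the doubling reported from the US trial.

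The cost is rewording and less favourable stated power, with no extra participants.
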